#### Quality assessment

It is possible that some **participants** known as ‘speeders’ may try to complete the DCE survey as soon as possible without seriously considering the survey questions. ‘Speeders’ will be identified as those who complete the survey at least 50% faster than the median time for survey completion among all valid survey respondents. We will then conduct a sensitivity analysis and determine whether or not the removal of identified speeders significantly alters the results.

We will also assess the possibility of order effect bias by introducing a dummy variable for the order of the choice set. We will test for left and right bias by including a constant for the left choice and examining the extent to which the left position of the alternatives in the choice sets influences the likelihood of being chosen. Comparable probabilities of the left and centre alternatives being selected would suggest the absence of bias.

### Sample size calculation

Given the absence of any DCE priors for sexual health preferences of older adults in the UK, we used the following parametric-based DCE sample size calculation formula:

$$n\geq \frac{1-p}{rpa^{2}}\times {\left[(\Phi {)}^{-1}⟮1-\frac{\alpha }{2}⟯\right]}^{2}$$

Equation 1: Parametric DCE sample size formula.^26^

Whereby *n* is the minimum sample size needed to detect *p*, the assumed true population probability of selecting uptake of sexual health services over ‘opt-out’, and whereby *r* is the number of choice sets that each individual completes, *a* is the level of precision around the assumed population probability, Ф^−1^ is the inverse cumulative normal distribution function and α is the significance level.^26^ Conservatively assuming that the true population probability of sexual health service uptake is 0.5 and assuming that each participant will complete eight choice sets, we estimate that a sample of 191 participants will be needed to generate a point estimate ±0.05 of the true population probabilities and with 95% confidence. However, to maintain power for two-group subgroup analyses, we will aim to recruit a total 240 participants including those from sexual minorities groups and disabled people.

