#### Pilot testing

We intend to use convenience sampling to recruit up to 30 participants for the pilot test. Participants in the pilot test will receive a £20 gift card for completing the survey. Conducting the pilot test will serve two purposes: (1) identify potential problems with the DCE and survey in general (eg, cognitive fatigue or incoherent questions or lack of accessibility) and (2) generate priors (ie, parameter estimates) that will be used to develop the design of the final full-scale DCE. We will analyse the pilot data with multinomial logit (MNL) models, given the limited sample size. Priors from the pilot test will be input into Ngene to finalise and enhance the efficiency of the full-scale DCE design.

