### Statistical analysis

We will use descriptive statistics to summarise the key sociodemographic characteristics of the study population. We will assess sexual health service preferences and preference heterogeneity using MNL, latent class and mixed logit (MXL) models. While the MNL is the starting point for most discrete choice models, it suffers from some unrealistic assumptions, particularly around unobserved heterogeneity. The MXL model can accommodate unobserved heterogeneity. The MXL analysis will be conducted with 1000 Halton draws and will assume normally distributed preference heterogeneity for each attribute level. We will assess for unobserved heterogeneity by examining the statistical significance of the SD of the random parameters in the MXL model. We will calculate the relative importance and predicted probabilities of opt-out for select sexual health service scenarios. We will assess how sexual health service and message sharing preferences could vary among those willing and unwilling to use sexual health services by using interaction terms for sociodemographic characteristics.

We will perform latent class analyses to elucidate if there are unobserved groups of people with similar preferences for use of sexual health service.^27^ First, we will conduct a latent class conditional logit model that includes individual characteristics and attribute level preferences.^27^ Selection of individual characteristics will be determined by expert opinion and findings from the formative qualitative interviews. Second, we will determine the optimal number of subgroups by comparing the Bayesian information criterion (BIC) values of 2, 3, 4, 5, 6 and 7-class models and each models’ interpretability and class size distribution.^27^ Lower BIC values indicate better model fit. Third, we will use descriptive statistics to characterise each class based on their members’ preferences and characteristics. All analyses will use effects coding and be weighted to reflect the population of middle-aged and older adults in the UK.

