#### Attribute relative importance and probability of opt-out

For each of the sex-class combinations, the relative importance of each attribute will be calculated by dividing the range of the parameter estimates of a given attribute by the summation of the ranges of all attributes.^28^

We will further illustrate potential preference heterogeneities by using equation 2 to calculate the predicted probabilities of selecting ‘opt-out’ over select sexual health service scenarios for each sex-class combination. Specifically, the predicted probability of a participant choosing alternative *i* over alternative *j* can be estimated by dividing the exponentiated summation of coefficients for scenario *i* by the exponentiated summation of coefficients for scenario *j*.

$$\text{Pi}=\frac{e^{\beta x_{i}}}{\sum e^{\beta x_{j}}}$$

Equation 2: Predicted probability of selecting alternative *i* within a two-alternative choice set'.

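### The sample size and its ±0.05 precision refer only to the overall uptake share, not to the coefficients, relative importance or scenario probabilities that the analysis will report

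*Protocol article*

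**What the plan says.** The section on sample size calculation (protocol article) uses a published formula for discrete choice experiments. Its target, p, is "the assumed true population probability of selecting uptake of sexual health services over ‘opt-out". The inputs are given as "Conservatively assuming that the true population probability of sexual health service uptake is 0.5" and "assuming that each participant will complete eight choice sets". The conclusion is that "a sample of 191 participants will be needed to generate a point estimate ±0.05 of the true population probabilities and with 95% confidence". The target is then raised: "to maintain power for two-group subgroup analyses, we will aim to recruit a total 240 participants". No calculation accompanies that step. The reason given for choosing this formula is that no priors exist for this population.

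The results are described elsewhere. Under Statistical analysis: "We will assess sexual health service preferences and preference heterogeneity using MNL, latent class and mixed logit (MXL) models", with latent class models of 2 to 7 classes. Under Attribute relative importance and probability of opt-out, relative importance is computed for each sex-class combination, and the authors will "calculate the predicted probabilities of selecting ‘opt-out’ over select sexual health service scenarios for each sex-class combination". Under Pilot testing, priors do become available, and their stated use is the design: "Priors from the pilot test will be input into Ngene to finalise and enhance the efficiency of the full-scale DCE design".

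**The concern.** The quantity that was sized is not among the quantities that answer the study's question. Equation 1 contains p, r, a and α. It would give the same n for two attributes or twenty. The second objective concerns which features of a service matter, and that is answered by attribute-level coefficients and what is derived from them. A half-width on a probability has no meaning for a logit coefficient or for a relative importance. A scenario opt-out probability does lie on the probability scale, but it depends on the opt-out constant and on a coefficient from every attribute, so its precision differs from that of an average share.

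Two things are at stake. A reader who meets ±0.05 for population probabilities, in the plural, may carry it over to the scenario probabilities. And with no detectable effect stated, an attribute level with a small effect could be reported as unimportant without anyone knowing how likely the study was to find it.

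**Working it through.** **1. The plan's own figure.** Inputs from the sample size section: p = 0.5, r = 8, a = 0.05, α = 0.05.

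n ≥ (1 − p)/(r·p·a²) × z² = 0.5/(8 × 0.5 × 0.0025) × 1.96² ≈ 192.07, against 191 printed. The difference is immaterial.

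**2. What a means.** Over n people and r independent choices, the share has standard error √[p(1 − p)/(rn)]. Solving Equation 1 for a gives z√[(1 − p)/(p·r·n)], which is that error times z, divided by p. So a is relative to p.
- n = 191: a = 0.050, or 0.050 × 0.5 = ±0.025 absolute.
- n = 240: a = 0.045, or ±0.022 absolute.
- Absolute ±0.05 would need p(1 − p)z²/(r × 0.05²) = 48.02, so 49 people.

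With within-person correlation ρ, the variance is multiplied by 1 + 7ρ. For an assumed ρ of 0.1 to 0.5, the absolute half-width at 240 is ±0.029 to ±0.047.

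**3. Scenario opt-out probability, pooled.** Assumptions not in the article: six layouts of 4 to 8 attributes with 2 to 4 levels; D-efficient designs of 32 sets; two services plus opt-out; an opt-out constant of ln 2 (with zero main effects, 2/(2 + 1 + 1) = 50% opt-out); MNL; independent choices. Effects coding and eight sets per person are the plan's own. For one scenario against opt-out, with η the opt-out constant minus the sum of that scenario's coefficients and P = 1/(1 + e^(−η)), the half-width is 1.96 × SE(η) × P(1 − P). The table shows the median over random scenarios. The columns for 120 and 60 people are the 240 column times √2 and 2.

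| Attributes × levels | 240 (pooled) | 120 | 60 |
|---|---|---|---|
| 4 × 2 | ±0.035 | ±0.049 | ±0.070 |
| 6 × 2 | ±0.040 | ±0.057 | ±0.080 |
| 4 × 3 | ±0.047 | ±0.066 | ±0.094 |
| 6 × 3 | ±0.056 | ±0.079 | ±0.112 |
| 8 × 3 | ±0.064 | ±0.091 | ±0.128 |
| 6 × 4 | ±0.069 | ±0.098 | ±0.138 |

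Pooled at 240, three of the six layouts meet ±0.05. A second set of assumptions (4 to 6 three-level attributes, moderate coefficients) gave ±0.035 to ±0.081 pooled.

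**4. Sex-class combinations.** Two equal classes by two equal sexes give 240/4 = 60 per cell. If each cell is fitted separately, the last column applies: ±0.07 to ±0.14. If class coefficients are shared across sexes, about 120 people inform each class: ±0.05 to ±0.10, and only the 4 × 2 layout just meets ±0.05. More classes widen these figures.

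**5. Power for one coefficient at 240**, as Φ(β/SE − 1.96), same assumptions:

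| Effects-coded coefficient | 3-level attribute | 4-level attribute |
|---|---|---|
| 0.10 | about 53% | about 37% |
| 0.15 | about 87% | about 68% |
| 0.20 | about 98% | about 90% |

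**The case against.** A reader might infer that the protocol promises ±0.05 for every scenario and sex-class cell and fails to deliver it. The text does not support this. It defines p as the overall share, and no precision figure is attached to coefficients, relative importance or cells. The plural in the precision sentence is loose wording. That reading also fails numerically for pooled scenarios, since half of the layouts tried meet ±0.05 at 240.

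Nor do the documents show that 240 is too small. About even odds of detection arises only for a coefficient of 0.1 on a three-level attribute. At 0.2, power is at least about 90% for both three-level and four-level attributes. The documents state no effect size of interest.

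It is also fair to say that coefficient-based sizing was not possible before the pilot, that a pilot of up to 30 people gives imprecise priors, and that the sex-class probabilities are meant to illustrate heterogeneity in an exploratory study. Using the priors for the design alone is not an error, and an article may leave a later recalculation to the full protocol.

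These points limit the concern but do not remove it. The article makes one affirmative precision statement, it concerns a quantity that is not among the planned results, and its ±0.05 is not what Equation 1 computes.

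**Conclusion.** The point holds as a mismatch between what was sized and what will be reported, together with an imprecise statement about the share itself. The mismatch can be read directly from the text and needs no modelling assumption. So can the relative meaning of a, which makes the figure about ±0.025 absolute at p = 0.5 and 191 people with independent choices.

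The size of the gap is illustrative. It is nil to moderate for pooled scenarios and clear for most sex-class results, even with only two classes. It rests on assumed attribute and level counts, equal classes and sexes, efficient designs and independent choices. Independence is the favourable case: the plan expects preference heterogeneity and weights its analyses, and both would generally widen the intervals. This calls for a correction to the stated precision, not for a larger study.

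**What to change.** - State that the Equation 1 figure applies only to the overall uptake share and that a is relative, about ±0.025 absolute at p = 0.5. Drop ±0.05 as a statement about the population probabilities.
- Keep the target of 240.
- After the pilot, take the covariance matrix of the final Ngene design at the pilot priors, with a range around those priors because the pilot has at most 30 people. From it, state for 240 participants (a) the smallest attribute-level coefficient detectable with 80% power, and (b) the 95% half-width of the planned scenario opt-out probabilities, pooled and by sex-class combination.
- Report intervals with all scenario probabilities, and label sex-class results exploratory where the half-width exceeds 0.05.

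The cost is a change of wording and one calculation from output that the pilot and design steps already produce. No extra participants are needed. The downside is that the stated precision becomes less favourable, and some sex-class results will carry the exploratory label.

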### Statistical analysis

We will use descriptive statistics to summarise the key sociodemographic characteristics of the study population. We will assess sexual health service preferences and preference heterogeneity using MNL, latent class and mixed logit (MXL) models. While the MNL is the starting point for most discrete choice models, it suffers from some unrealistic assumptions, particularly around unobserved heterogeneity. The MXL model can accommodate unobserved heterogeneity. The MXL analysis will be conducted with 1000 Halton draws and will assume normally distributed preference heterogeneity for each attribute level. We will assess for unobserved heterogeneity by examining the statistical significance of the SD of the random parameters in the MXL model. We will calculate the relative importance and predicted probabilities of opt-out for select sexual health service scenarios. We will assess how sexual health service and message sharing preferences could vary among those willing and unwilling to use sexual health services by using interaction terms for sociodemographic characteristics.

We will perform latent class analyses to elucidate if there are unobserved groups of people with similar preferences for use of sexual health service.^27^ First, we will conduct a latent class conditional logit model that includes individual characteristics and attribute level preferences.^27^ Selection of individual characteristics will be determined by expert opinion and findings from the formative qualitative interviews. Second, we will determine the optimal number of subgroups by comparing the Bayesian information criterion (BIC) values of 2, 3, 4, 5, 6 and 7-class models and each models’ interpretability and class size distribution.^27^ Lower BIC values indicate better model fit. Third, we will use descriptive statistics to characterise each class based on their members’ preferences and characteristics. All analyses will use effects coding and be weighted to reflect the population of middle-aged and older adults in the UK.

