### Phase II—discrete choice experiment survey

Second, we will use the qualitative information from Phase I to inform what attributes (characteristics) and levels (choices) will be included in the unlabeled choice set, which will be administered in an online survey to a sample of older adults to identify their preferences for accessing sexual health services. We will design choice sets composed of hypothetical sexual health service delivery scenarios. Similarly, as stated for the interview, we will employ the same strategy to recruit disabled people and people from sexual minority groups for the survey to allow subanalyses of the results. We will aim to have disabled people and sexual minorities make up 10% each out of the total sample size.

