### Developing the DCE design

#### Pictorial representation of attribute levels and DCE choice set size

A ranking exercise will be organised with some of the interview participants to align and finalise the attributes and levels that will be included in the final choice sets (online supplemental appendix III). After attributes and levels have been finalised, we will generate visual graphics to represent each attribute level in the DCE survey (see online supplemental appendix IV for a sample). To ensure that the visual graphics effectively represent the intended meaning of each attribute level (ie, construct validity), we will conduct qualitative think-aloud, pilot exercises with up to 10 individuals from the target population, including disabled people and those from sexual minority groups and participants will provide feedback about how they interpret and feel about the graphics.^24^ This will be an iterative process with the draft pictorial concepts being tested until they are appropriately representing the intended concept. DCE surveys tend to present between 4 and 18 choice sets. During these interviews, we will also explore the optimal number of choice sets to present to each respondent to manage potential cognitive fatigue. Similar to the phase 1 interviews, participants will be purposively selected across different locations, age range, ethnic backgrounds and disability status. Again, reasonable accommodation will be made to promote inclusion of disabled persons, although people with severe cognitive/intellectual impairment will not be included in this step. Recruitment will be through collaborations with community-based organisations with which our research team already have existing research collaborations with.

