#### Full-scale DCE survey

Community-based organisations, local clinics, GP practices and older people care homes will be contacted to help distribute the online survey. Recruitment will be carried out purposively from urban and suburban areas, evenly spread across varying gender mix and the middle age and older adults age groups. We will create formats for completing the DCE surveys both online and offline.

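### The planned sociodemographic interaction terms cannot separate a difference in preferences from a difference in choice consistency, so a noisier group with identical preferences can appear to have weaker ones

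*Protocol article*

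**What the plan says.** All references are to the protocol article.

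- **Purpose of the comparison.** Disabled people and sexual minorities are recruited "for the survey to allow subanalyses of the results" (Phase II—discrete choice experiment survey), each at a target of 10% of the sample. The Sample size calculation section sets the total at 240.
- **Method.** The Statistical analysis section assesses preferences and their heterogeneity "using MNL, latent class and mixed logit (MXL) models". Variation in preferences is to be examined "by using interaction terms for sociodemographic characteristics". The mixed logit "will assume normally distributed preference heterogeneity for each attribute level". No scale parameter is named.
- **Summaries.** In the section on attribute relative importance and probability of opt-out, relative importance is obtained by "dividing the range of the parameter estimates of a given attribute by the summation of the ranges of all attributes", for combinations of sex and latent class. Predicted opt-out probabilities follow: "We will further illustrate potential preference heterogeneities by using equation 2".
- **Response quality.** Interviews will explore "the optimal number of choice sets to present to each respondent to manage potential cognitive fatigue". On mode of completion: "We will create formats for completing the DCE surveys both online and offline". The Quality assessment section adds a sensitivity analysis without very fast respondents, applied to the sample as a whole.

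**The concern.** The question is whether preferences differ between groups. In a logit model the coefficients are identified only as preference multiplied by scale, where scale is the inverse of the error spread. Apart from an exact offset between the two, an attribute-by-characteristic interaction is zero only if both preference and scale are equal in the groups compared. The null hypothesis it tests is therefore narrower than equal preferences.

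If one group answers less consistently, all its coefficients shrink towards zero together. The interactions then look like weaker preferences for every attribute that matters. The study's purpose is to help tailor services to older people and to specific groups within that population. A group could be described as caring less about service features when it only answered with more noise.

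Unequal consistency is plausible here. The article recruits across age and disability status and through care homes, tests for cognitive fatigue and lack of accessibility, and offers more than one format. It does not say that any group will answer more noisily.

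**Working it through.** **The plan's own figure.** Equation 1 with p = 0.5, r = 8, a = 0.05 and z = 1.96 gives 0.5 / (8 × 0.5 × 0.05²) × 1.96² = 50 × 3.8416 = 192.08, against the stated 191. The difference is trivial and does not bear on this point. What carries over is the target of 240, eight choice sets per person, and a 10% quota of 0.10 × 240 = 24, leaving 216.

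**Algebra.** Let group g have preference weights β_g and scale λ_g. The fitted coefficient is λ_g β_g and the interaction is δ = λ₂β₂ − λ₁β₁. With identical preferences and λ₁ = 1, δ = −(1 − λ)β, where λ is the scale ratio. This is non-zero for every attribute level with a non-zero weight.

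**Worked example (assumed weights).** Take four three-level attributes with effects-coded levels b, 0 and −b, where b = 0.6, 0.4, 0.3 and 0.2, and an opt-out constant of −0.5.

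- Coefficients at λ = 0.5: 0.60 becomes 0.30 and 0.40 becomes 0.20. A large-sample fit gave 0.29 and 0.20.
- Opt-out against the best scenario: the utility gap is 0.6 + 0.4 + 0.3 + 0.2 + 0.5 = 2.0. At λ = 1 the probability is 1/(1 + e²) = 0.12. At λ = 0.5 it is 1/(1 + e) = 0.27. The planned opt-out probabilities therefore move with scale.
- Relative importance: the ranges are 1.2, 0.8, 0.6 and 0.4, which sum to 3.0, giving 0.40, 0.27, 0.20 and 0.13. Halving every range leaves these unchanged, so this summary is scale-free.

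**Simulation.** Inputs from the article are N = 240, eight sets per person and the 10% quota. Inputs assumed here are two services plus opt-out, four or five three-level effects-coded attributes, a strongest level effect of about 0.6, independent choices, and the scale ratio itself. Preferences are identical in both groups. The test is a joint likelihood-ratio test of all group interactions at 5% (9 or 11 degrees of freedom). Ranges are across the assumed designs; a single figure means one design was run.

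| Scale ratio | Rejects, 120 v 120 | Rejects, 216 v 24 |
|---|---|---|
| 1.0 | 3.5% to 5.5% | 4.5% to 6% |
| 0.9 | 7.5% to 9.6% | 4% to 8.5% |
| 0.8 | 17.5% to 29% | 7.5% to 11.6% |
| 0.7 | 47% to 53.5% | 19.2% to 19.6% |
| 0.6 | 85% to 91% | 35% |
| 0.5 | 96% to 99% | 57% to 59% |

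Most settings used 200 to 400 runs. At 400 runs the simulation standard error at 50% is √(0.5 × 0.5/400) = 2.5 points. With all level effects halved, the 120 v 120 rates were 24.5% at 0.7 and 44.5% at 0.6.

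**With one free relative scale parameter** (one degree of freedom fewer), the same comparison rejected 2.4% to 7.5% across these settings. When two attributes' weights were truly swapped between groups of 120, it kept 99% to 100% power.

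**Two limits of that test.**

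- In 216 v 24 with equal scale, swapping the weights 0.6 and 0.4 between groups was detected in only 26% of runs.
- With normal heterogeneity between individuals (SD 0.5 per coefficient), equal mean preferences and equal scale, the simple multinomial version rejected 15% (120 v 120) and 18% (216 v 24). The interaction test rejected 14% and 18%. Ignoring repeated choices by the same person inflates both tests.

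**The case against.** **A condensed article may leave scale specification to an analysis plan.** An analysis plan that is not shown could add a scale term. The article nevertheless names a tool for a stated question, and that tool does not isolate what the question asks. The point concerns the named method, not a missing detail.

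**The article states no joint test, no significance level for the interactions and no rule for declaring a difference.** This is correct. The percentages show how far the tool can mislead if used in the usual way; they do not predict what will be reported. The sentence on interactions is also loosely worded, since it contrasts willing and unwilling users but names sociodemographic terms. The scale problem applies on either reading.

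**The scale ratio is assumed.** This also stands. Several of the cited features, such as pilot testing, alt-text, the choice of number of sets and offline formats, are measures to reduce noise. A reader might infer that disabled or older respondents will answer less consistently, or that such groups will be reported as having different preferences. The article supports neither inference. With 24 people in a subgroup and a modest gap, most interaction tests would not reject.

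**Relative importance is already planned.** It is scale-free, but it is defined for combinations of sex and class and is not set beside the interaction terms. The mixed logit describes variation between individuals and does not separate a group shift in scale from one in preference. The check on fast respondents is not group-specific.

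**A scale test could mislead in the other direction.** Reading non-rejection as proof that only consistency differs would be unsound. Power is low in the quota groups, and a purely proportional difference cannot be assigned to either source. The fix has to respect this.

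**Conclusion.** The point holds as a limit on interpretation that the plan should address. The interaction terms test equality of preference multiplied by scale, and nothing in the article separates the two for the groups compared. With identical preferences and N = 240, the joint 5% test rejects about 18% to 29% at a scale ratio of 0.8 and about 50% at 0.7 for equal groups. For a 10% subgroup the rates are about 8% to 12% and 20%. At 0.9 or above they are close to nominal.

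These figures rest on the assumed designs, effect sizes, independent choices and scale ratios. They establish that a false appearance of weaker preferences is possible and, for balanced groups with a clear scale gap, likely. They do not establish that such a gap exists in this population, or that the study will misreport any group.

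**What to change.** In the Statistical analysis section, add for each characteristic compared:

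1. Fit a model with common preferences and a group-specific scale parameter, and compare it with the interaction model. Use the Swait-Louviere likelihood-ratio test, or its equivalent in a model that allows for repeated choices per respondent.
2. Report scale-free quantities by group (relative importance or coefficient ratios, with confidence intervals) beside the interaction coefficients. This extends the relative-importance section beyond combinations of sex and class.
3. Where common preferences with a free scale are not rejected, state that the data do not distinguish a difference in preferences from one in choice consistency. Do not label it as either.

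The cost is one extra model fit and one parameter per characteristic, with no new data. The downside is low power in the 10% subgroups. A difference that is proportional across all attributes would also stay unattributed, which is what such data can support.
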